### *Standard of Care – DVT/VTE Prophylaxis*

For patients admitted to an Adult Medicine Service, the order set prompts the following calculation of the Padua risk tool for VTE prognostication:

▼ DVT/VTE Prophylaxis

▼ Adult DVT/VTE Prophylaxis

☒ VTE Prophylaxis Orders - Patient Service Considered Adult Medicine

☒ VTE Prophylaxis (Padua) Panel

☒ [figure not shown] VTE risk score not documented

If patient is currently on therapeutic anticoagulation, a Padua risk score is not required at this time.

Otherwise, please calculate the Padua risk score for all adult medicine patients and choose the risk stratification below.

**Padua Risk Score**

|                                                                                 |   |
|---------------------------------------------------------------------------------|---|
| Active cancer (in previous six months)                                          | 3 |
| History of VTE                                                                  | 3 |
| Reduced mobility for at least three days                                        | 3 |
| Known thrombophilia (e.g. mutation, antiphospholipid antibody)                  | 3 |
| Trauma or major surgery in last month                                           | 2 |
| Heart or respiratory failure                                                    | 1 |
| Acute MI or ischemic stroke                                                     | 1 |
| Acute infection or rheumatologic disorder                                       | 1 |
| On estrogen therapy                                                             | 1 |
| Age greater than 70
(Age is 30 y.o.)                                         | 1 |
| BMI greater than 30
(There is no height or weight on file to calculate BMI.) | 1 |

If Padua risk score is **GREATER THAN OR EQUAL TO 4**, please order prophylaxis or select reason(s) for not ordering.  
If Padua risk score is **LESS THAN 4**, no prophylaxis needed at this time.

- ☐ On therapeutic anticoagulation (No Padua risk score needed)
- ☐ High risk - Padua risk score GREATER THAN OR EQUAL TO 4 (Prophylaxis recommended)
- ☐ Low risk - Padua risk score LESS THAN 4 (No prophylaxis needed at this time)

For patients not currently listed as admitted to Adult Medicine, admitting physicians are prompted to indicate if patients will be admitted to Adult Medicine, the service using the DVT/VTE prophylaxis order set:

▼ DVT/VTE Prophylaxis

▼ Adult DVT/VTE Prophylaxis

☒ [figure not shown] VTE Prophylaxis Orders - Patient Service Not Currently Considered Adult Medicine

Will this patient be admitted to one of the following **ADULT MEDICINE** services?

Cardiology  
Gastroenterology  
General Internal Medicine  
Geriatrics  
Hepatology  
Hematology  
Infectious Disease  
Nephrology  
Oncology  
Pulmonary

- ☐ YES - VTE Prophylaxis (With VTE Risk Score)
- ☐ NO - VTE Prophylaxis (Without VTE Risk Score)

Selecting Yes prompts the Padua risk tool as above.

Protocol Version #: 4

Protocol date last updated: 7/11/2025

VUMC IRB #241978

If the admitting physician selects “High Risk” on the Padua, they are prompted to select prophylaxis:

If they indicate a permanent contraindication “Order”, they are prompted to select the reason:

## Intervention

The CDS intervention will include EHR "nudges" in the form of Best Practice Advisories targeting those encounters on which 1) VTE-AI risk is above threshold (defined below), 2) no active DVT prophylaxis pharmacologic order is present, 3) no contraindication has been documented in the current admission order sets above. The schematic below demonstrates the implementation.

[figure not shown]

The CDS will prompt on order sign for admissions order sets (current state) and on Chart Review the subsequent morning for each day of an inpatient encounter. The CDS BPA is shown here and prompts consideration of pharmacologic prophylaxis and opportunities to take alternate actions including disagreeing with the alert, entering contraindications, or indicating the patient is already on acceptable prophylaxis.

Best Practice Advisory

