### 2.0 Rationale and Specific Aims

This study will rigorously study *novel AI approaches* to this *important diagnostic challenge* and produce strong evidence for the pragmatic use of novel AI-CDS to prevent HA-VTE across diverse sites and populations.

The goal of this study is to evaluate the effectiveness of AI-driven CDS to reduce the incidence of HA-VTE across two dimensions: urban (Vanderbilt Adult Hospital [VUH]) and rural (Vanderbilt Regional Health System [VRHS] including Vanderbilt Tullahoma Harton Hospital [VTHH], Vanderbilt Bedford County Hospital [VBCH], and Vanderbilt Wilson County Hospital [VWCH]).

We will implement a validated risk score, VTE-AI, which does not require clinician input to calculate, to prompt CDS suggesting reconsideration of DVT prophylaxis in those who 1) do not have active prophylaxis ordered and 2) have no contraindication to pharmacologic prophylaxis. This CDS "nudge" will occur after admission orders have been submitted for hospital admissions and on each subsequent day of an inpatient encounter.

The current standard of care is an order set requiring manual calculation of the Padua risk tool and selection of a prophylaxis option or documentation of a temporary or permanent exception. We will evaluate the effectiveness of the VTE-AI-driven clinical

decision support (CDS) against the standard DVT/VTE prophylaxis order set to reduce HA-VTE incidence across urban/rural dimensions.

Aim 1: Prospectively validate the VTE-AI risk score in clinical production systems. We hypothesize the VTE-AI risk score will be non-inferior in clinical production compared to the retrospectively validated model (benchmark c-statistic > 0.8)

Aim 2: Develop a modified, simplified version of the DVT/VTE order set that does not require manual calculation of the Padua risk tool (standard of care) and assess its acceptability with clinicians in trial sites.

Aim 3: Conduct pragmatic RCT of VTE-AI-driven CDS against standard of care at VUH and VTHH. We will implement CDS at VUMC and VTHH randomizing half the eligible encounters to CDS and half to standard of care.

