**Venous Thromboembolism (VTE) risk prediction**

[feedback](#)

- Patient at high predicted VTE risk.** 12% probability during this stay (>3.6% = high risk). [Model details](#).
- Consider ordering pharmacologic prophylaxis.** We did not identify any [contraindications](#) or active VTE prophylactic or therapeutic [orders](#).

Order

Do not order

VTE prophylaxis panel

Order

Do not order

Permanent contraindication to VTE prophylaxis for rest of encounter

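### As worded, the alert's contraindication check refers to the admission order sets, although the alert can fire on every later inpatient day

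*Protocol*

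**What the plan says.** Section 2.0 (Rationale and Specific Aims) aims the nudge at patients who lack active prophylaxis and who "have no contraindication to pharmacologic prophylaxis". It has the nudge occur once admission orders are in and "on each subsequent day of an inpatient encounter".

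Section 6.0 (Intervention) turns this into three firing conditions: VTE-AI risk above threshold; "no active DVT prophylaxis pharmacologic order is present"; and "no contraindication has been documented in the current admission order sets above". It then states when the alert appears: on signing the admission order sets, and "on Chart Review the subsequent morning for each day of an inpatient encounter". On how this is built, it says "The schematic below demonstrates the implementation"; that figure does not appear in the text available here.

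The alert display in section 6.0 tells the clinician: "We did not identify any [contraindications](#) or active VTE prophylactic or therapeutic [orders". The same display lets the clinician enter a permanent contraindication for the rest of the encounter, or choose a 24 or 48 hour delay for a temporary one. Under Discontinuing Interventions, acting on any of the buttons ends the alert.

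**The concern.** The firing schedule runs through the whole stay, but the contraindication condition points to documents completed at its start. Contraindications to anticoagulant prophylaxis can develop in hospital, and a new bleed is the obvious case. A rule that consults only admission entries would not register it.

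What is at stake is the harm that section 7.0 names: bleeding when prophylaxis is ordered because of the prompt and would not otherwise have been. A clinician could be steered towards prophylaxis, and told that no contraindication was identified, for a patient who has since acquired one. This concerns the safety specification of the intervention, not the trial's inference.

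**Working it through.** The Protocol gives no figure for this point, so the check sets its statements side by side and then follows one patient through them.

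**1. Scope of each statement.**

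| Place in Protocol | What is tested or asserted | Limit on source |
|---|---|---|
| Section 2.0 | patient has no contraindication | none stated |
| Section 6.0, Intervention, third condition | none documented | the admission order sets |
| Section 6.0, alert display | none identified | none stated |

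The middle row defines when the alert fires, and it is the narrowest of the three.

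**2. Tense and location.** The second condition is a current-state test: it asks whether an order is active now. The third, in the same sentence, asks whether something has been documented in a named place. Nothing in the sentence says that it is re-evaluated against later entries.

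**3. One patient (illustrative).** Take a patient in the decision-support arm whose VTE-AI risk stays above threshold. Prophylaxis is ordered at admission, stopped on day 3 for bleeding, and the reason is entered outside the admission order sets.

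| Time | Risk above threshold | No active prophylaxis order | No contraindication in admission order sets | Alert as worded |
|---|---|---|---|---|
| Admission to day 3, before the stop | yes | no | yes | held back |
| Next morning | yes | yes | yes | can fire |

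Because the second condition held the alert back until then, no button had been used. Neither the alert's contraindication entries nor its stop rule had come into play.

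**4. After that firing.** The clinician can enter a permanent contraindication or choose a delay, and firing then stops or is postponed. The gap is therefore mainly the first firing after the contraindication arises, together with any contraindication never entered through the alert.

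**5. Does it touch the sample size?** The inputs under Sample Size are 4.3% against 2.2%, 80% power and 5% type I error (taken as two-sided), with equal arms. With pooled variance and p̄ = (0.043 + 0.022)/2 = 0.0325:

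n = [1.960·√(2·0.0325·0.9675) + 0.842·√(0.043·0.957 + 0.022·0.978)]² / (0.043 − 0.022)² = (0.4915 + 0.2107)² / 0.000441 ≈ 1,118.1

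This rounds up to 1,119 per arm, against the stated 1,118. The population in that calculation is defined by high predicted risk and absence of pharmacologic prophylaxis. The third condition is not one of its inputs, so rewording it changes none of these numbers.

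**6. Frequency.** The Protocol does not give the share of encounters in which a contraindication first arises after admission, so the number of affected alerts cannot be calculated.

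**The case against.** The strongest reply is that the sentence is not the build. The Protocol refers the reader to a schematic, and neither that figure, the order-set screens nor the lists linked from the alert can be seen here. The sentence does not contain the word only and sets no time limit. It can fairly be read as naming the kind of structured entry that suppresses the alert, namely the contraindication order in the standard-of-care order sets, whenever that entry is made. This stands as a limit: the documents do not show that the running alert ignores later contraindications. It does not remove the mismatch, because the sentence as written is still narrower than section 2.0 and the alert display.

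A second reply is that the alert has its own contraindication route. That is right for later firings, but the route opens only once the alert has fired, so it does not cover the first one.

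A third reply is that harm is well contained. The alert orders nothing by itself, the decision stays with the practitioner (section 6.0, concomitant care), and the study team reviews bleeding rates every three months (section 8.0, Auditing). This also stands, and it keeps the point minor.

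A reader might go further and infer either of two things that the documents do not support:

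- **That a temporary exception entered at admission silences the alert for the whole stay.** Section 2.0 says the order set takes "selection of a prophylaxis option or documentation of a temporary or permanent exception", but how long a temporary entry lasts would be on screens not shown, and the alert's own temporary options expire.
- **That patients on therapeutic anticoagulation go unscreened**, because the second condition mentions only prophylaxis orders. The alert display says therapeutic orders are searched as well.

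**Conclusion.** The point holds as a minor, inexpensive safety correction. As worded, the third firing condition refers to contraindications in the admission order sets while the alert can fire on each later inpatient day, which is narrower than both the stated target and what the clinician is told.

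The practical effect depends on one assumption: that the build follows the sentence. If it does, a contraindication that arises after admission and is entered elsewhere does not suppress the first alert that follows. If the build already screens the whole encounter, the only error is in the sentence.

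The size cannot be calculated from the documents. A reader might infer that the trial comparison is biased or underpowered as a result; nothing in the Protocol supports that, and no effect on power, type I error or bias is claimed.

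**What to change.** In section 6.0 (Intervention), reword the third condition along these lines: *at each firing, no active contraindication recorded in the current encounter as a structured entry (admission order sets, later contraindication orders, or alert responses)*. Naming the entry types matters, because a rule that refers to documentation anywhere in the encounter cannot be built without knowing which fields to read.

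Align section 2.0 and the alert display with that wording, so that the clinician is told what was searched. Which conditions count as contraindications remains for the clinical team.

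If the build already works this way, correct the section 6.0 sentence and leave the logic alone. Otherwise the cost is the text edit plus a small change to the trigger logic. The downsides are slightly fewer alerts, and that contraindications charted only in free text are still not caught.

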**Venous Thromboembolism (VTE) risk prediction**

[feedback](#)

- Patient at high predicted VTE risk.** 12% probability during this stay (>3.6% = high risk). [Model details](#).
- Consider ordering pharmacologic prophylaxis.** We did not identify any [contraindications](#) or active VTE prophylactic or therapeutic [orders](#).

Order

Do not order

VTE prophylaxis panel

Order

Do not order

Permanent contraindication to VTE prophylaxis for rest of encounter

**Acknowledge Reason**

Delay 24 hrs - Temporary contraindication

Delay 48 hrs – Temporary contraindication

Remind me next time I open orders

I disagree

Patient is already on anticoagulation

This alert is presenting as part of a randomized controlled trial and does not fire for all patients at increased VTE risk. More information related to this trial can be found at [clinicaltrials.gov/NCT06939803](https://clinicaltrials.gov/NCT06939803). VUMC IRB 241978.

**Accept**

**Dismiss**

### Discontinuing Interventions

The CDS will be discontinued by acting on any of the above buttons in the BPA, the Recommended or Alternate Actions.

### Adherence to Intervention Protocols

Protocol Version #: 4

Protocol date last updated: 7/11/2025

VUMC IRB #241978

Adherence to the primary intervention will be measured through direct interaction with the study decision support tools. We will also assess orders for all patients randomized in the trial to verify whether prophylaxis orders were made as well as data from admitting orders and existing BPAs related to VTE prophylaxis.

#### *Relevant concomitant care and interventions*

Decision to act on study CDS is left to practitioners in study settings. Any concomitant care is permitted at any point in the trial and during study encounters.

#### *Participant Timeline*

Randomization, interventions, and assessments all occur within each study encounter with no follow-up or additional interventions for either study participants (practitioners) or patients.

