### *Secondary Objective*

We hypothesize the VTE-AI CDS will not increase bleeding risk, readmission rates, or lengths of stay (LOS) between the intervention and non-intervention arms.

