### *Primary Outcome/Endpoint*

Incidence of HA-VTE, VTE associated with healthcare encounter. We will exclude VTE present on admission (VTE-POA) as a study outcome.

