### *Secondary Outcomes/Endpoints*

Secondary trial outcomes include process metrics – Length of Stay, Readmission Rates – and safety metrics – bleeding events. Length of Stay is measured as days between admission and discharge. Readmission Rates will be rates of readmission within 30-days of discharge for trial encounters related to VTE. Bleeding events are a safety risk from anticoagulation and DVT/VTE prophylaxis and will be monitored during the trial.

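### The protocol rules out follow-up after the encounter yet names a 30-day readmission outcome, and limiting that outcome to VTE means it cannot test the hypothesis that readmissions do not increase

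*Protocol*

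**What the plan says.** Four places in the protocol bear on what is observed and for how long.

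- **Section 6.0, Participant Timeline:** "Randomization, interventions, and assessments all occur within each study encounter with no follow-up or additional interventions". The sentence applies this to patients as well as practitioners.
- **Section 6.0, Secondary Outcomes/Endpoints:** "Readmission Rates will be rates of readmission within 30-days of discharge for trial encounters related to VTE". Bleeding is listed separately: "Bleeding events are a safety risk from anticoagulation and DVT/VTE prophylaxis and will be monitored during the trial".
- **Section 2.1, Secondary Objective:** the hypothesis is that the CDS "will not increase bleeding risk, readmission rates, or lengths of stay (LOS"), compared between arms. Readmission is not restricted by cause.
- **Section 6.0, Primary Outcome/Endpoint:** "Incidence of HA-VTE, VTE associated with healthcare encounter", followed by "We will exclude VTE present on admission (VTE-POA) as a study outcome". No diagnosis window is given.

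Two further places help in reading these. Section 12.0 refers to outcome data collection at the conclusion of the trial period, based only on EHR queries. The advisory shown to clinicians expresses risk over the stay: "12% probability during this stay (>3.6% = high risk").

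**The concern.** The protocol fixes an assessment period that ends with the encounter and an outcome that begins at discharge. Both cannot be followed as written.

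The readmission outcome also does not match its objective. The objective is a no-harm claim, and the harm that Section 7.0 names is bleeding from prophylaxis that would not otherwise have been ordered. An outcome confined to VTE-related readmission looks where the intervention is expected to help. If the CDS works, this measure falls, and it could be reported as support for no increase in readmissions while readmissions for bleeding or other causes went unexamined.

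Finally, the primary endpoint has no window of its own, so the timeline sentence is the only text that could supply one. Read that way, HA-VTE diagnosed after discharge would not count in the primary endpoint. The protocol does not say whether this is intended, or whether the 4.3% baseline was counted the same way.

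**Working it through.** **1. Assessment period against the readmission outcome.** The timeline places assessments inside the encounter. The readmission window runs from discharge to day 30, entirely after it. The two do not overlap, so one statement must change. Section 12.0 shows that a passive look-back is foreseen, which points to the timeline sentence as the one that is badly worded. No section says how long after the last discharge the query is run. If it ran on the day the trial period closed, encounters discharged in the final month would have less than 30 days observed. At the 150 to 230 encounters per month and one-year duration in Section 10.0, and assuming a steady discharge rate, that is 150 to 230 encounters, or 1/12 = 8.3% of the total.

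**2. Readmission outcome against the objective.** Write the arm difference (CDS minus control) in 30-day readmission rate, by main cause, as

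Δ(all-cause) = Δ(VTE) + Δ(bleeding) + Δ(other).

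The Secondary Objective concerns the left-hand side. The outcome, on its natural reading, observes only Δ(VTE). If the CDS does what the primary objective hopes, Δ(VTE) is zero or negative. If extra prophylaxis causes harm, Δ(bleeding) is positive. A negative Δ(VTE) is compatible with any value of Δ(all-cause), so the measure cannot support the objective. The documents give no readmission rates, so no numerical size can be put on this.

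**3. Primary endpoint window.** First, the plan's own figure. Inputs from Section 10.0: p1 = 0.043, p2 = 0.022, 80% power, type I error 5% (taken as two-sided, since sidedness is not stated). With pooled variance under the null and no continuity correction:

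n = [1.960·√(2·0.0325·0.9675) + 0.8416·√(0.043·0.957 + 0.022·0.978)]² / (0.021)² = (0.4915 + 0.2107)² / 0.000441 ≈ 1,118.1.

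This is 1,119 per arm when rounded up, against the stated 1,118. Power at 1,118 per arm is 80.0%. The stated sample size reproduces.

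Whether the window matters for power depends on how 562/12,946 was counted, which the protocol does not say.

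- If 4.3% is already an in-stay rate, an in-stay endpoint leaves power unchanged.
- If 4.3% includes VTE found after discharge and the trial counts in-stay events only, both rates shrink. Assume a share f of events surfaces after discharge and the relative effect is unchanged. The rates become 0.043(1−f) and 0.022(1−f):

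| f (assumed) | Rates | Power at 1,118 per arm | n per arm for 80% |
|---|---|---|---|
| 10% | 3.87% vs 1.98% | 75.6% | 1,247 |
| 20% | 3.44% vs 1.76% | 70.4% | 1,408 |
| 30% | 3.01% vs 1.54% | 64.5% | 1,614 |
| 50% | 2.15% vs 1.10% | 50.1% | 2,275 |

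The values of f are assumptions that illustrate why the window should be stated. They are not estimates of a loss in this trial.

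**The case against.** The strongest defence is that the timeline sentence means only that nobody is contacted or treated after the encounter. Read with Section 12.0, readmissions would be found by query and nothing is lost. That is a fair account of the likely intent, and it defeats the inference that the readmission outcome is unmeasurable. It does not make the sentence correct, because the sentence covers assessments as well as interventions.

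A second defence is that bleeding is its own safety outcome, with rates reviewed every three months under Auditing in Section 8.0. A reader might infer that bleeding after discharge is never counted. The documents do not say so: the bleeding outcome is not expressly limited to the stay. What stands is narrower. Bleeding readmissions are outside the readmission measure, and the bleeding outcome has no stated post-discharge window.

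Third, the phrase about VTE could attach to the trial encounters and not to the readmissions. That reading is possible but less natural, and an outcome definition open to both needs rewording in any case.

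Fourth, a reader might infer that VTE surfacing after discharge is lost altogether, being excluded as present on admission at the second encounter. The protocol does not state this. The primary endpoint excludes only VTE present on admission, which is naturally read at the index admission, and a VTE that brings the patient back within 30 days would appear in the secondary readmission outcome. An in-stay primary endpoint would also match the horizon shown in the advisory, so it could be a legitimate choice. It needs to be stated.

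**Conclusion.** Two points hold on the text. The no-follow-up statement contradicts the 30-day readmission outcome. It is a wording conflict that Section 12.0 makes easy to resolve. The readmission outcome, on its natural reading, counts only the readmissions that prophylaxis should reduce and so cannot support the hypothesis of no increase in readmission rates. This second point is the more important, because following the plan exactly would give a measure that points only in the favourable direction.

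A third point holds conditionally. The primary endpoint has no ascertainment window, and if the timeline is taken literally, HA-VTE diagnosed after discharge does not count in it. The sample size arithmetic is sound. Any loss of power depends on two things the protocol does not give: whether the 4.3% includes post-discharge events, and what share they are.

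A reader might go further and conclude that in-stay capture is biased through length of stay. The protocol gives no ground to expect lengths of stay to differ between arms, so that is not claimed here.

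**What to change.** 1. **Participant Timeline:** say that there is no patient contact or intervention after the encounter, but that outcomes are extracted passively from the EHR through 30 days after discharge. Set the data cut no earlier than 30 days after the last discharge, and align Section 12.0.
2. **Secondary Outcomes:** define readmission as all-cause readmission within 30 days of discharge, with VTE-related and bleeding-related readmission as components. The all-cause measure then matches the Secondary Objective, and the components show benefit and harm separately. State the window for the bleeding outcome.
3. **Primary Outcome:** state the ascertainment window, say whether the 562/12,946 baseline was counted over the same window, and state that the present-on-admission exclusion applies at the index admission.

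The cost is some rewording, a broader query of EHR data and a data cut 30 days later. Readmissions outside the health system would remain unseen under either wording, and the report should say so. All-cause readmission will also include many events unrelated to prophylaxis, which is why the two components should be reported beside it.
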